### Neuroimaging data analysis

We will process the GRE data to generate QSM maps using the standard pipeline implemented in the SuscEptibility mapping PIpeline tool for phase (SEPIA) images toolbox run under MATLAB (MathWorks, Natick, MA), following established methodologies (38). Whole-brain magnitude images will be skull-stripped using the BET tool from the FMRIB Software Library, integrated within the MEDI toolbox. The overall procedure consisted of three main steps: (1) Total field recovery will be achieved through echo phase combination via the optimum weights method (39), followed by phase unwrapping using SEGUE (40). (2) Background field removal will then be performed on the unwrapped phase images by applying the Laplacian boundary value approach (41). (3) Finally, quantitative susceptibility maps will be reconstructed using the STAR-QSM algorithm for dipole inversion (42).

Region-of-interest (ROI) definition and extraction will follow an *a priori*, region-based approach. We will focus on deep grey matter and limbic structures that are susceptible to post-stroke iron accumulation and implicated in cognition, including the bilateral caudate nucleus, putamen, globus pallidus, thalamus, hippocampus, red nucleus, substantia nigra, and dentate nucleus, informed by previous QSM studies of brain iron and clinical outcomes (43–46). For each participant, the T1-weighted structural image will be co-registered to the QSM map, and subcortical ROIs will be segmented using a standard atlas-based method implemented in FSL. The resulting ROI masks will be resampled into QSM space and visually inspected. Mean susceptibility values (ppm) within each ROI will be extracted at baseline and at week 4. All registrations and ROI segmentations will be visually checked by two independent neuroimaging analysts. Any discrepancies will be resolved by consensus, and if necessary, the processing pipeline will be refined before final extraction. All image preprocessing and QSM analyses will be performed on de-identified datasets that are coded by study ID, and the analysts will remain blinded to treatment allocation and clinical outcome data until the primary analyses have been completed.

Statistical analysis will be performed in SPSS 26.0 (IBM, Armonk, NY, USA). Within-group changes in susceptibility (post–pre) are tested with paired-samples *t*-tests, and between-group differences are assessed with independent-samples t-tests. Pearson correlation coefficients will be calculated to examine associations between changes in ROI-based susceptibility and corresponding changes in cognitive, functional, emotional, and sleep measures; if normality is violated for either variable, Spearman’s rank correlation will be used. Data normality will be assessed with the Shapiro–Wilk test. Two-sided *p*-values of < 0.05 will be considered statistically significant, and false-discovery-rate correction will be applied across the predefined ROIs to control for type I error. Given the 4-week interval and modest imaging sample size, the QSM substudy is not powered to detect small absolute susceptibility changes. We will therefore focus on within-subject changes in ROI-based susceptibility and on medium-to-large associations with cognitive outcomes, interpreting all imaging findings as exploratory.

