### Sample size

This exploratory trial was primarily designed to estimate effect sizes and assess protocol feasibility. Consistent with pilot-trial recommendations for acupuncture and traditional Chinese medicine (22, 23), we set the target sample size at 30 participants per arm. Allowing for an anticipated 20% attrition, we therefore planned to enroll 36 participants in each group (total *n* = 72). For the MRI substudy, we will randomly select 15 participants per arm (*n* = 30) from the clinical cohorts, in line with Desmond and Glover’s guidance on imaging sample sizes (24). Under a two-tailed *α* = 0.05, this total sample provides approximately 80% power to detect medium-to-large correlations (r ≥ 0.50) between QSM-derived susceptibility measures and cognitive outcomes, based on Fisher’s z transformation in G*Power 3.1. Smaller associations will be interpreted with caution, and the MRI substudy is therefore primarily intended to provide preliminary estimates of effect sizes and variance components to guide the design of future, adequately powered imaging trials. With 15 participants per arm, the substudy will also have approximately 80% power to detect between-group differences in 4-week changes in regional susceptibility of approximately 0.8 standard deviations (Cohen’s d), whereas smaller treatment effects on QSM will be treated as exploratory and described descriptively.

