Continuous variables will be presented as mean ± standard deviation (SD) when normally distributed or median with an interquartile range (IQR) for non-normally distributed data. Between-group comparisons will utilize independent samples t-tests for normally distributed variables and Mann–Whitney U-tests otherwise. Within-group pre-post comparisons will use the Wilcoxon signed-rank test. Correlation analyses will preferentially apply Pearson’s method; if either variable violates normality, Spearman’s rank correlation will be substituted. To control for confounders, covariates including age, sex, education level, stroke severity (baseline NIHSS score), and time from stroke onset to enrolment will be incorporated into multivariable linear regression models to evaluate between-group differences in the primary endpoint and key secondary cognitive outcomes. Where available, additional vascular and imaging-related factors, such as stroke subtype, lesion side, and vascular territory, lesion volume, baseline white matter hyperintensity burden (e.g., Fazekas score), receipt of intravenous thrombolysis, and major vascular comorbidities, will be explored as candidate covariates in sensitivity analyses.

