Iron is an essential micronutrient in the brain, involved in neurotransmitter synthesis, myelin formation, and mitochondrial energy production (54, 55). However, ischemic stroke can disrupt iron homeostasis, resulting in excess iron accumulation in affected and connected brain regions and triggering iron-dependent oxidative neurotoxicity (ferroptosis) (56, 57). Radiological and histopathological studies have demonstrated progressive iron deposition in structures such as the ipsilateral thalamus, substantia nigra, and basal ganglia after stroke, and higher post-stroke iron burden in deep grey matter has been linked to poorer neurological outcomes (57–59). The degree of post-stroke iron accumulation in these regions correlates with worse neurological outcomes (56, 58, 59). These observations support cerebral iron overload as a clinically relevant, potentially modifiable factor in post-stroke recovery and provide a rationale to investigate brain iron as a mechanistic target in PSCI.

QSM is a gradient-echo based MRI post-processing technique that reconstructs tissue magnetic susceptibility maps from phase images. Because paramagnetic iron is a major source of susceptibility contrast in the brain, higher QSM values closely reflect increased regional iron content and have been widely used to characterize iron accumulation in brain aging, neurodegenerative diseases, and cerebrovascular disorders (44, 60, 61). In patients with acute IS, a recent QSM study reported that higher iron content in deep grey matter nuclei was associated with poorer functional outcome (43), supporting cerebral iron burden as a clinically meaningful imaging marker in this population. These advances indicate that QSM provides a quantitative and relatively specific *in vivo* measure of brain iron load, making it particularly suitable for testing ferroptosis-related hypotheses in PSCI. However, the magnitude and time course of intervention-related changes in QSM after stroke are not yet established in humans. In this trial, QSM outcomes will therefore be treated as exploratory mechanistic markers to provide effect-size estimates and generate hypotheses.

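### The QSM regions are not aligned to the side of the infarct, although the iron rationale rests partly on ipsilateral deposition; a treatment effect confined to the lesion side would be roughly halved in the raw mean

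*Protocol article*

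**What the plan says.** The Discussion describes "progressive iron deposition in structures such as the ipsilateral thalamus, substantia nigra, and basal ganglia after stroke". Just before that it makes a wider statement, that ischaemic stroke disturbs iron balance, "resulting in excess iron accumulation in affected and connected brain regions".

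The Neuroimaging data analysis section sets the regions of interest in advance as eight paired structures, "including the bilateral caudate nucleus, putamen, globus pallidus, thalamus, hippocampus, red nucleus, substantia nigra, and dentate nucleus". The measure is then defined: "Mean susceptibility values (ppm) within each ROI will be extracted at baseline and at week 4". For the change in susceptibility, "between-group differences are assessed with independent-samples t-tests", and changes are correlated with changes in the cognitive and other scales. A false-discovery-rate correction runs across the predefined regions. The text does not say whether the left and right members of a pair are combined.

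Lesion side appears once, in Clinical data analysis, in a list of further factors "such as stroke subtype, lesion side, and vascular territory, lesion volume". These are candidate covariates for sensitivity analyses, to be used where available. The eligibility criteria do not restrict the side of the infarct. The imaging subgroup excludes left-handed patients.

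On size, the Sample size section says "we will randomly select 15 participants per arm (*n* = 30) from the clinical cohorts". It gives the purpose of the substudy as supplying preliminary effect sizes and variance components for later imaging trials.

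**The concern.** Part of the stated mechanism is lateralised relative to the infarct, but the planned regions are anatomical. Without a label tied to the infarct, each region mixes patients or tissue on the lesion side with patients or tissue on the other side. If left and right are pooled, the mixing is within each patient. If they are kept apart, it is between patients, because the left thalamus is ipsilesional in some and contralesional in others.

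A treatment effect that followed the lesion side would then be estimated too small. The main product of the substudy is a set of effect sizes for planning the next trial, so an attenuated estimate goes straight into that use. A null result would also be hard to read: it could mean no effect, or an effect on one side only. The optional lesion-side covariate does not solve this. It belongs to the clinical analysis, and a main-effect term for side would not realign the hemispheres in the imaging t-tests.

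**Working it through.** **Inputs from the protocol.** 15 participants per arm; two-sided alpha 0.05; target between-arm difference d = 0.8 in four-week change (Sample size).

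**Assumptions, not in the documents.** The treatment effect is 0.8 SD on the lesion side and zero on the other. The left-right correlation of change is rho. The share of patients whose lesion lies on a given side is q. The change has SD 1 on each side.

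**The plan's own figure.** The Sample size section claims about 80% power for d = 0.8 with 15 per arm. The noncentral t (28 degrees of freedom, noncentrality 0.8 × sqrt(15/2) = 2.19) gives 56%, so the claim does not reproduce. That is a separate matter. It is used here only as the starting point: 56% is the power for a region coded to the lesion side under the assumptions above.

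**Reading A: left and right averaged.** The mean effect is d/2 = 0.40. The SD of the average is sqrt((1 + rho)/2). So d_eff = 0.40 / sqrt((1 + rho)/2).

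| rho | d_eff | share of 0.8 kept | power |
|---|---|---|---|
| 0 | 0.57 | 71% | 32% |
| 0.3 | 0.50 | 62% | 26% |
| 0.5 | 0.46 | 58% | 23% |
| 0.7 | 0.43 | 54% | 21% |
| 1 | 0.40 | 50% | 18% |

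**Reading B: left and right kept as separate regions.** The mean effect in one region is q × d. The variance in the active arm is 1 + q(1 − q)d², in the sham arm 1, and the SD is pooled over arms. For q = 0.5: mean 0.40, active-arm variance 1 + 0.25 × 0.64 = 1.16, pooled SD sqrt((1.16 + 1)/2) = 1.039, d_eff = 0.40/1.039 = 0.385.

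| q | mean effect | d_eff | share of 0.8 kept | power |
|---|---|---|---|---|
| 0.4 | 0.32 | 0.31 | 39% | 13% |
| 0.5 | 0.40 | 0.38 | 48% | 17% |
| 0.6 | 0.48 | 0.46 | 58% | 23% |

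The raw mean is halved in Reading A, and in Reading B when q = 0.5. The loss in Reading B comes almost wholly from the mean: the extra between-patient variance raises the SD by only about 4% (1.039 against 1).

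**If the contralesional side also responds.** Let its effect be a fraction f of the ipsilesional one. Averaging gives d(1 + f)/2 / sqrt((1 + rho)/2). This exceeds d when f > sqrt(2(1 + rho)) − 1, which is 0.61, 0.73 and 0.84 for rho = 0.3, 0.5 and 0.7. Above those values the pooled region has more power than the ipsilesional region alone.

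**The case against.** A reader might infer that the protocol averages the two hemispheres. It does not say so. It covers both sides and extracts a mean within each region; if the sides are kept apart, relabelling them later needs no new data, and such labelling could sit in a fuller document. That stands, and it is why both readings are worked through. But the article does commit to the regions and to the tests, and neither is tied to the infarct.

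A reader might also infer that the protocol expects a one-sided treatment effect. It does not. The ipsilateral structures are examples of natural deposition, next to a wider statement about affected and connected regions. The link to functional outcome in the acute-stroke QSM study is stated for deep grey matter nuclei without a side. The stimulation is midline or bilateral, and the rationale includes systemic iron pathways. So the loss computed above is what would happen under one pattern, not a prediction.

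It would further be tempting to make the ipsilesional region the sole main test. The last step of the working shows that this can lose power if the other side also responds, and the documents give neither f nor rho. That objection succeeds, and the remedy below reports both sides instead.

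Finally, the imaging is declared exploratory throughout. This limits the weight of the point, since the MoCA endpoint is untouched. It does not remove it, because an exploratory label tempers p-values but does not correct an attenuated estimate.

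**Conclusion.** The point holds in conditional form. Part of the iron rationale is ipsilateral, while the imaging regions and tests ignore the side of the infarct and leave left-right pooling unstated. If the treatment effect is confined to the lesion side, the raw mean difference is about halved, and the standardised effect falls to 50–71% of its size (sides averaged, rho from 1 to 0) or about 39–58% (sides separate, q from 0.4 to 0.6). Power for a true lesion-side effect of 0.8 SD would fall from 56% to 18–32% or 13–23% respectively. These figures rest on a zero contralesional effect and on assumed values of rho and q. They cover the between-arm comparison only; no figure was derived for the correlations. The change is worth making before analysis because it costs little and because choosing the coding after seeing the data would be post hoc.

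**What to change.** In the Neuroimaging data analysis section:

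- Code each paired region as ipsilesional or contralesional to the qualifying infarct.
- Record lesion side for all 30 substudy participants, rather than where available. Patients with a previous stroke are already excluded, which makes the qualifying infarct easier to identify.
- Report the between-arm difference and the correlations for both sides, at least for the thalamus, substantia nigra and basal ganglia. A bilateral effect then shows in both, a one-sided effect in one.
- Keep the false-discovery-rate correction, applied across the resulting set of regions.
- Prespecify that bilateral and midline infarcts are reported separately.

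The cost is wording and one recorded variable; no scan is added. There are two small downsides. Patients with bilateral or midline infarcts leave the side-coded analysis, which trims a sample of 30. And the correction runs over more tests than if sides were pooled: with all eight structures coded, 2 × 8 = 16 regions instead of 8.

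### The imaging plan puts its focus on within-subject susceptibility change and larger associations, not on the EA-minus-sham contrast that alone separates EA from natural post-stroke iron change

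*Protocol article*

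**What the plan says.** The Sample size section of the protocol article takes the MRI participants from both arms: the investigators will "randomly select 15 participants per arm (*n* = 30) from the clinical cohorts". It describes the substudy as "primarily intended to provide preliminary estimates of effect sizes and variance components" for later imaging trials. It gives two power statements at about 80%: one for correlations of 0.50 or more in all 30 participants, and one for the arms, "approximately 80% power to detect between-group differences in 4-week changes in regional susceptibility of approximately 0.8 standard deviations".

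The Neuroimaging data analysis section sets the tests: "Within-group changes in susceptibility (post–pre) are tested with paired-samples *t*-tests, and between-group differences are assessed with independent-samples t-tests". Changes in regional susceptibility are then correlated with changes in the clinical scales, by Pearson or Spearman, with false-discovery-rate correction across regions. The section concedes that 4 weeks and a modest sample cannot detect small susceptibility changes, and draws a consequence: "We will therefore focus on within-subject changes in ROI-based susceptibility and on medium-to-large associations with cognitive outcomes". It ends by calling all imaging findings exploratory.

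The Discussion, on the background biology, reports "progressive iron deposition in structures such as the ipsilateral thalamus, substantia nigra, and basal ganglia after stroke".

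**The concern.** The focus sentence offers a remedy for low power that is not one. If the randomised comparison is imprecise, moving attention to change within an arm gains sensitivity only by giving up the control group. Participants enter 7 to 30 days after onset and are scanned again at week 4, a period in which the protocol itself expects iron to change. A paired test in the EA arm asks whether susceptibility moved, not whether EA moved it.

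The second half of the sentence has a related weakness. The main product of the substudy is meant to be effect-size estimates for later trials. Estimates brought forward because they came out large are too large on average.

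At stake is the mechanistic message. A significant paired test under EA beside a non-significant one under sham is easily read as evidence of mechanism, although it is not a test of the difference. A later trial designed on a size-selected correlation would be too small.

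**Working it through.** **Inputs from the protocol:** 15 participants per arm, 30 in all; two-sided alpha 0.05; paired t-tests within arms, independent t-tests between arms, correlations of changes. **Assumed:** the size of the natural drift, in SDs of the change score (0.3, 0.5, 0.8), because the documents give none; normal data; all 30 analysable.

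**1. The plan's own correlation figure.** Fisher z: power = Φ(atanh(r)·√(n−3) − 1.960). For r = 0.50, n = 30: 0.549 × √27 = 2.854; 2.854 − 1.960 = 0.894; Φ(0.894) = 0.814. The stated figure of about 80% is reproduced.

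**2. Equal drift in both arms, no EA effect.** Paired t-test with n = 15: 14 degrees of freedom, noncentrality d·√15. The probability p that one arm is significant comes from the noncentral t. The two arms are independent, so the chance that EA is significant and sham is not is p(1 − p).

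| Assumed drift (SD) | Noncentrality | EA-arm paired test significant | EA significant, sham not | Between-arm t-test significant |
|---|---|---|---|---|
| 0.3 | 1.16 | 19% | 0.192 × 0.808 = 16% | 5% |
| 0.5 | 1.94 | 44% | 0.438 × 0.562 = 25% | 5% |
| 0.8 | 3.10 | 82% | 0.821 × 0.179 = 15% | 5% |

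These are rates per region before false-discovery-rate correction. The correction would change them but does not address the problem: under drift the within-arm null hypothesis is false, so a rejection is a correct answer to a question that is not about EA.

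**3. Selection by size.** 200,000 simulated bivariate-normal samples of n = 30. The critical |r| at p < 0.05 is 0.361.

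| True r | Mean r, all reported | Mean \|r\| if only p < 0.05 is highlighted | Mean \|r\| if only \|r\| ≥ 0.50 is highlighted |
|---|---|---|---|
| 0.2 | 0.196 | 0.45 | 0.56 |
| 0.3 | 0.295 | 0.47 | 0.57 |
| 0.4 | 0.394 | 0.50 | 0.58 |
| 0.5 | 0.493 | 0.54 | 0.60 |

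With a threshold of 0.50, the highlighted values hardly depend on the truth, so they say little to a later trial. With everything reported, the bias is negligible.

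**4. Arm and onset time in the correlations.** A drift common to everyone adds a constant and leaves r unchanged, so step 2 does not carry over to the correlations. Two other routes do. Time from onset varies over 7 to 30 days and may drive both iron change and cognitive recovery; the Clinical data analysis section adjusts its models for it, while the imaging correlations are unadjusted. Pooling the arms can also create correlation. If EA shifted both measures by an assumed 0.8 SD through unrelated routes, with no within-arm association, equal arms would give a between-arm covariance of 0.8²/4 = 0.16 and pooled r = 0.16/1.16 = 0.14.

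**The case against.** The strongest reply is that the between-arm test is already planned, in the same sentence as the paired tests, and removes drift common to both arms. Within-subject change may also simply mean the change scores which that test compares. No passage attributes within-arm change to EA. Medium-to-large can be read as the range the substudy is powered for, not a reporting filter: the Sample size section says smaller associations will be read cautiously and smaller treatment effects reported as description. All imaging results are labelled exploratory. A change-score t-test is valid under randomisation, so ANCOVA is a gain in precision, not a correction of an error.

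Most of this stands, and it limits the point to what the focus sentence puts first. What remains is that the plan runs both tests and then says which result gets the attention, and on its ordinary reading that is not the randomised one. If only change scores were meant, the sentence is ambiguous and needs the same rewording. The exploratory label limits the claims; it does not remove confounding from a within-arm result or selection from an estimate passed on. Keeping smaller associations in view is also not a commitment to report every estimate.

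**Conclusion.** The point holds as a matter of emphasis and wording. The plan puts within-subject change and larger associations in front, where the randomised contrast and complete reporting belong. Under the assumed equal drift, the misleading pattern of EA significant and sham not would appear in roughly 15% to 25% of trials per region, uncorrected, against 5% for the between-arm test. If associations were highlighted only at |r| ≥ 0.50, a true 0.3 would appear as about 0.57.

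A reader might go further and infer that the analysis will present natural iron change as an EA effect and will inflate its effect sizes. The documents do not support that: the between-arm test is planned, no such attribution is made, and inflation arises only if reporting is selective, which is not announced. A reader might also infer that left and right regions are pooled in a way that dilutes an effect on the lesion side. The text lists bilateral structures without saying how sides are combined, and an article may leave that to the full plan.

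**What to change.** Reword the focus sentence in Neuroimaging data analysis along these lines:

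- The lead imaging result for every region is the between-arm difference in week-4 susceptibility, adjusted for baseline susceptibility by ANCOVA, with its 95% CI.
- Within-arm changes are shown descriptively, without tests.
- Every region-by-outcome association is reported with its CI whatever its size, from a regression or partial correlation adjusted for arm and time from onset.

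No new data are needed: baseline susceptibility and time from onset are already to be recorded. The cost is one degree of freedom for the baseline term and two for arm and onset time in the association models. The rewording does not cure the low power. With 15 per arm and d = 0.8, the noncentrality is 0.8 × √7.5 = 2.19, and a two-sided t-test on 28 degrees of freedom has about 56% power, not the stated 80%. That mismatch is a separate matter, but it means the lead intervals will be wide and should be presented as such.
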